# Study Schema
[figure not shown]

# Introduction

##

## B.1 Background and Rationale

The role of ultrasound in bedside patient assessment has expanded drastically over the past two-decades. In particular, technological advances in recent years – which have considerably reduced the size and cost of ultrasound devices – have expanded the availability of ultrasound beyond the confines of formal diagnostic laboratories.^1–3^ Due to the significant difficulty, and unreliability, of cardiovascular assessment, bedside cardiac ultrasound – coined focused cardiac ultrasound (FoCUS) – is increasingly being incorporated into the routine evaluation for cardiac pathology.^3,4^

While several societal guidelines have outlined the recommended elements of a FoCUS assessment, perhaps none is most important than evaluation of left ventricle (LV) systolic function.^5–8^ Formal evaluation of LV systolic function, with transthoracic echocardiography (TTE), is assessed through measuring the difference between the end-diastolic and end-systolic volumes of the LV, and dividing by the end-diastolic volume – thereby calculating the left ventricular ejection fraction (LVEF).^9^ Calculating LV volumes through 2D linear measurements (i.e. Teichholz and Quinones methods) are not recommended due to the potential for significant inaccuracy as a result of the geometric assumptions required with these methods. Rather, the American Society of Echocardiography recommends that, when using 2D echocardiography, LV volumes are measured using the biplane method of disks summation (modified Simpson’s rule), whereby the LV cavity is traced in the apical four- and apical two-chamber views at end-systole and end-diastole.^9^ These volume measurements can then be applied, as described above, to calculate the LVEF, as well as to estimate the stroke volume and cardiac output. Hemodynamic parameters such as stroke volume and cardiac output can also be obtained from invasive right heart catheterizations. During a right heart catheterization, pressure measurements are obtained via a pulmonary artery catheter inserted via the right jugular vein.

While the modified Simpson’s rule is the ideal method for evaluation of LVEF from 2D images, this has been either not possible (i.e. small screen sizes and inability to perform frame-by-frame measurements) or not practical (i.e. insufficient training) when performing a FoCUS assessment. As a result, to date, we have relied on visual LVEF evaluation as part of the FoCUS examination. Although there is evidence of good correlation between visual estimation of LVEF, this is highly dependent on the level of training and expertise of the individual capturing and interpreting the images and vulnerable to subjective bias.^2^

To overcome this obvious limitation there has been significant interest in automating the assessment of LV systolic function through incorporation of artificial intelligence (AI) into point-of-care ultrasound devices. Several devices with AI have received FDA and Health Canada approval and early studies have demonstrated very good correlation between non-experts assessment of LVEF with that of experts.^10^ Although these early results are promising, there have been no adequately powered, real-world, clinical studies assessing the accuracy of AI LVEF detection.

Presently, the attending physicians, fellows, and residents at Tufts Medical Center have been using the KOSMOS (EchoNous, Redmon, WA) portable ultrasound device to perform FoCUS assessments as part of routine patient care, including utilization of the automated LVEF, stroke volume, and cardiac output features. This information is incorporated into the overall clinical diagnosis and decision-making process, much like the information obtained from the patient’s history and physical examination.

- 1. This is not the first time the study drug, device, or intervention/procedure will be used in humans
  2. Is there an active control group?

**Yes  No**

If **Yes**, respond to all of the following:

1. *Check to confirm that* *the active control is an established effective intervention. If it is not, clarify how it is ethically justified to use this control in the study:*
2. *Describe any potential bias in the selection of the active control such that there will be an unfair advantage for the investigational intervention. For example, is the active control treatment known to be significantly less effective in this study population than another treatment:*       or

N/A

1. *Check to confirm that the sample size and the randomization ratio for this active control study is ethically justified with regard to the number of participants who will be exposed to the risks of the study.*

## B.2 Risks to Subjects

- 1. List the reasonably foreseeable risks, discomforts, hazards, and/or inconveniences to the subjects related to their participation in the research, including risk of unintentional loss of confidentiality. Include a description of the probability, magnitude, duration, reversibility, and potential consequences of the risks. Consider physical, psychological, social, legal, and economic risks:
- This study involves no more than minimal risks, as the study intervention is a non-invasive FDA-approved ultrasound examination. Records identifying study participants will be kept confidential and, to the extent permitted by the applicable laws, will not be disclosed or made publicly available, except as described in the consent document. De-identified data from this study may be used for future research purposes. Even though the likelihood that someone may identify participants from the study data is very small, it can never be completely eliminated – therefore there is a minor risk of loss of confidentiality.
  1. State which study interventions may have unknown risks:       or N/A
  2. State which study interventions may have risks to an embryo or fetus (if a subject is or becomes pregnant) or to a nursing infant of a study subject:       or N/A
  3. Describe risks to people other than the participating subject, e.g., risks to family members, friends, others or risks to the community:       or  N/A
  4. Are there any risks to study investigators or staff performing the study procedures due to research with high risk populations (e.g. prisoners, intravenous drug users, patients with major psychiatric issues, etc.):?

**Yes  No**

If **Yes**, respond to all of the following:

- 1. *Describe these risks:*
  2. *Describe the procedures that will be put in place to minimize these risks:*
  3. *Describe how these procedures are adequate for the location where study procedures will be performed:*
  4. *Check to confirm that you have contacted research administration to clarify whether additional approvals (e.g. Security, Risk Management, etc.) are needed for the performance of this study with high risk populations.*

## B.3 Potential Benefits to Subjects

- 1. Describe the potential benefits that individual subjects may experience from taking part in the research. Include the probability, magnitude, and duration of the potential benefits:
  2. Check if there is no direct benefit.
  3. Describe any benefit to the population from which the subject is drawn:
- We hope the information learned from this study will help us determine whether the results obtained from a portable ultrasound are reliable, and can, possibly, replace the need for obtaining a formal echocardiogram and/or right heart catheterization for some patients in the future.
  1. Describe any benefit to science, society, and humanity in general:       or  NA

##

## B.4 Alternatives

1. Describe alternatives to participating in this research study (e.g. to decide not participate in the study, alternative treatments, no treatment (palliative care), etc.):

Participation in this research is completely voluntary. The alternative to participating is to not participate. In either case all participants will receive standard of care medical treatments.

1. Describe the standard clinical care that may be an alternative:       or  N/A
2. Describe how the subject can receive the research procedures/drug/device used in this study in a non-research setting:       or  N/A

# Objectives

1. Describe the purpose, specific aims, or objectives of the study (i.e. the reason for performing the study in terms of the scientific question to be answered):

The aim of this study is to evaluate the accuracy of the KOSMOS portable ultrasound automated LVEF, stroke volume, and cardiac output detection in a real-world, clinical setting. We hypothesize that automated results will demonstrate a strong correlation with formal TTE and right heart catheterization studies.

- The primary outcome of interest is the overall diagnostic accuracy of the automated LVEF, stroke volume, and cardiac output computation as compared to either TTE (for LVEF assessments) or right heart catheterization (for stroke volume and cardiac output assessments).
- The secondary outcome of interest is time to LVEF acquisition with FoCUS

#

# Enrollment and Withdrawal

## D.1 Inclusion Criteria

- 1. Describe the criteria that define who will be **included** in the study as a numbered list:
- All patients who are cared for at Tufts Medical Center and:
  - Provide informed consent
  - Age greater than or equal to 18 years old
  - Undergo bedside FoCUS examination with the KOSMOS portable ultrasound device
  - Have had a TTE within 30 days, or have had a TTE ordered by the primary treating team and/or have had/are scheduled for a right heart catheterization with calculation of stroke volume and cardiac output

##

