## D.3 Withdrawal of Subjects

1. *Describe anticipated circumstances under which subjects will be withdrawn from the research without their consent:*

As the only intervention in this research study is the performance of a bedside cardiac ultrasound, which will take place as soon as possible after consent has been obtained, we do not anticipate any subjects being withdrawn from the research without their consent. If for some reason the patient’s primary treating physician determines that it is in the patient’s best interests to be withdrawn from the study then they will need to notify they study team, at which point the patient will be removed from the study.

1. *Describe procedures that will be followed when subjects withdraw or are withdrawn from the research, including the possibility of partial withdrawal from study intervention with continued data collection:*

If a participant is withdrawn from the study or chooses to stop being in the study, it will not affect their care or treatment outside this study. Any data collected prior to withdrawal will still be used for the study.

1. *Describe any necessary safety precautions to be applied to subjects who withdraw or are withdrawn (tapering drug doses, evaluative x-ray, etc.):*       or N/A

##

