## F.2 Procedures

1. If **Yes**, respond to all of the following:
2. *Describe the scientific, methodological, and medical reasons to use a placebo:*
3. *Describe the care that will be given to subjects who receive placebo. If this is local standard of care, specify that:*
4. *Describe all potential risks to the placebo group and how the risks will be minimized.*
5. *Summarize the research design and sequentially identify all procedures to be performed to accomplish the specific aims of the project. Clearly identify and distinguish procedures that are considered experimental, procedures that are performed exclusively for research purposes (including “extra” routine tests), and procedures that would occur regardless of the research (i.e., standard of care). Point out any procedures, situations, or materials that may be hazardous, and the precautions to be exercised to maintain subject safety:*

This is a prospective cohort study. Consecutive patients cared for at Tufts Medical Center, who have had a recent (within 30 days), or are scheduled to have a subsequent TTE performed at the discretion of the treating team will be screened for participation. Also, patients who are undergoing a right heart catheterization for a clinical indication will also be eligible for recruitment.

We will prospectively collect baseline clinical and demographic characteristics at the time of enrollment. We will be accessing the electronic medical record (Sorian) and entering the information collected into RedCap. There will be no collection of data beyond the date of enrollment, with the exception of those patients whose TTE or right heart catheterization has yet to be performed, in which case the subsequent TTE/right heart catheterization report will be the only information collected prospectively beyond the day of enrollment. The specific procedures to be followed will be:

- Patients who have had a recent TTE (within 30 days), or are scheduled to have a TTE and/or right heart catheterization performed for clinical reasons are eligible to participate in this study.
- If agreeable to participate in the study then participants will receive the usual standard of care (right heart cath and/or TTE) as dictated by the treating medical team.
- Upon signing the consent form, the research team will begin to collect baseline clinical and demographic information about participants from them and/or their medical chart.

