- Participants will then undergo the KOSMOS ultrasound evaluation at the time of enrollment or the earliest convenient time after enrolling in the study.
- The TTE and/or right heart catheterization data will be collected and compared with the results of the KOSMOS ultrasound.

*Please also describe the following concerning procedures:*

- - - - 1. How individuals will be screened for eligibility. Specify screening that will take place prior to informed consent and screening that will take place after informed consent:

Screening will begin through identifying individuals who are scheduled to undergo transthoracic echocardiogram and/or right heart catheterization at Tufts medical center. Patients who have recently underwent an echocardiogram may also be included if they are identified by the study team as potentially eligible for participation. There will be no additional screening prior to consent. Following consent the patient’s medical history will be evaluated by questioning the patient and, when necessary, reviewing the patient’s medical records for exclusion criteria. If no exclusion criteria are identified at this point then the patient will begin the protocol as described above.

- - - - 1. Procedures being performed to monitor subjects for safety or to minimize risks:

All data collected will be documented in the case report form in RedCap, which is stored on the Tufts secure server.

- - - - 1. All drugs and devices used in the research, their regulatory approval status, and the purpose of their use:

The KOSMOS device used in this project is an FDA approved ultrasound device that is available for commercial sale. It will be used to perform the bedside cardiac ultrasound as discussed above.

- - - - 1. The source records that will be used to collect data about subjects. (Attach all surveys, scripts, and data collection forms.):

See attached RedCap CRF

1. Is there a placebo control arm?

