**Yes  No**

Describe the following concerning pregnancy testing and birth control:

- - 1. What type of pregnancy testing and how frequently will be conducted on women of reproductive potential. If testing will not be conducted provide the reason: NA
    2. What birth control methods **women** of reproductive potential will be instructed to use. If women will not be instructed about acceptable methods of birth control, clarify why: NA
    3. What birth control methods **men** of reproductive potential will be instructed to use. If men will not be instructed about acceptable methods of birth control, clarify why: NA
  1. Describe the data that will be collected during the study and how the data will be obtained:

Following identification of the study cohort (as described above), clinical data will be abstracted from the electronic medical record (Sorian) including: demographic characteristics (i.e. sex, age, height, weight, body mass index), cardiac risk factors (i.e. hypertension, diabetes, smoking, hyperlipidemia, previous myocardial infarction, previous cardiac intervention, previous strokes, heart failure, etc.), past medical history, indication for FoCUS assessment and TTE.

- - 1. If there are plans for long-term follow-up (once all research related procedures are complete), describe the data will be collected during this period:       or  N/A
  1. Specify which tests are routinely performed for clinical care, but are providing data for the research, and which tests are only performed for research purposes:

All of the formal echocardiogram and right heart catheterization tests are performed for clinical care. The bedside cardiac ultrasound is also performed to guide clinical care, primarily through its ability to provide real-time results at the time of patient evaluation. However, in the case of participants who present for an outpatient right heart catheterization and/or echocardiogram, the bedside ultrasound would not be performed for clinical care, rather, in this group of participants, the bedside ultrasound would be performed specifically for research purposes.

- 1. For Humanitarian Use Device (HUD) uses provide a description of the device, a summary of how you propose to use the device, including a description of any screening procedures, the HUD procedure, and any patient follow-up visits, tests or procedures.      or  N/A

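### Only a past TTE has a time limit relative to the KOSMOS scan; a scheduled TTE and any right heart catheterization have none, so true change between tests is read as device error

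*Protocol*

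**What the plan says.** Eligibility (Protocol, D.1) offers two routes. The TTE route is "Have had a TTE within 30 days, or have had a TTE ordered by the primary treating team". The 30 days apply to the completed TTE; nothing limits the ordered one. The catheterization route is "and/or have had/are scheduled for a right heart catheterization with calculation of stroke volume and cardiac output", with no interval before or after the scan.

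F.2 repeats the TTE rule for patients "who have had a recent (within 30 days), or are scheduled to have a subsequent TTE performed at the discretion of the treating team". For catheterization it says only that "patients who are undergoing a right heart catheterization for a clinical indication will also be eligible for recruitment". It does not mention a past catheterization, which D.1 admits.

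The scan is tied to enrollment. F.2 places it "at the time of enrollment or the earliest convenient time after enrolling in the study", and D.3 says it is something "which will take place as soon as possible after consent has been obtained". Where the reference result is not yet available, F.1 and F.2 have it taken later from the medical record, with no cut-off.

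I.2 includes every enrolled patient except those found after enrollment to have moderate or greater regurgitant valve disease. It works with FoCUS-minus-TTE differences for LVEF and FoCUS-minus-catheterization differences for stroke volume and cardiac output. It specifies a Bland-Altman plot with bias and 95% limits of agreement for LVEF only.

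**The concern.** A method-comparison study reads the paired difference as measurement disagreement. That holds only if the quantity measured has not changed between the two measurements. Here the design admits pairs separated by up to 30 days (past TTE) or by any length of time (future TTE, past or future catheterization), and the analysis has no step that separates true change from device error.

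The population makes change plausible. D.4.1 recruits from medical, surgical and intensive care inpatients as well as from patients presenting for a test. On the KOSMOS scan, F.2 states that "The bedside cardiac ultrasound is also performed to guide clinical care", except in outpatients attending for a test, so management may change between scan and reference. G.7 says instead that the study will not affect clinical care. Those two statements should be reconciled, but the point does not depend on which is right.

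At stake is the primary outcome, the accuracy of automated LVEF, stroke volume and cardiac output. B.3 hopes the results will show whether the device could replace formal echocardiography or catheterization for some patients.

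**Working it through.** **1. Intervals allowed by the text**

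| Reference test | Limit before scan | Limit after scan | Source |
|---|---|---|---|
| TTE | 30 days | none | D.1, F.2 |
| Right heart catheterization | none | none | D.1 |

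No other section supplies a limit. Recruitment when patients present for the test (D.4.1) makes same-day pairs possible but does not require them.

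**2. The plan's own figures**

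The sample sizes in I.2 follow from the precision of a single proportion at 95% confidence (the confidence level is assumed; it is not stated): n = 1.96² × p(1 − p) / d².

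- LVEF, p = 0.95, d = 0.05: 3.8415 × 0.0475 / 0.0025 = 72.99, rounded up to 73, as stated.
- Stroke volume and cardiac output, p = 0.90, d = 0.10: 3.8415 × 0.09 / 0.01 = 34.57, rounded up to 35, as stated.

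Both reproduce, so the issue is design and not arithmetic. Neither calculation allows for change between tests.

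**3. What enters the difference**

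For one pair, FoCUS − reference = device bias + device error ± true change. The sign is plus if the reference came first and minus if it came later. If true change is independent of device error,

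SD of differences = sqrt(SD_device² + SD_change²) = SD_device × sqrt(1 + r²), with r = SD_change / SD_device.

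The protocol gives neither SD, so r is an assumption:

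| r | sqrt(1 + r²) | Widening |
|---|---|---|
| 0.25 | 1.03 | 3% |
| 0.5 | 1.12 | 12% |
| 0.75 | 1.25 | 25% |
| 1 | 1.41 | 41% |

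The LVEF limits of agreement widen by the same factor. For stroke volume and cardiac output the factor applies to the SD of the differences.

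**4. If only some pairs are separated in time**

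Suppose, as a further assumption, that half the pairs have negligible change. The factor becomes sqrt(1 + r²/2): sqrt(1.125) = 1.06 at r = 0.5 and sqrt(1.5) = 1.22 at r = 1, that is 6% and 22%.

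**5. Effect on the agreement proportion used for sizing**

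I.2 does not define agreement. Suppose it means a difference within a fixed tolerance, with normal differences, zero bias and change in every pair. The observed agreement is then 2Φ(z / sqrt(1 + r²)) − 1, with z = 1.96 for 95% and 1.645 for 90%.

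| True agreement | Observed, r = 0.5 | Observed, r = 1 | Evaluable n for the stated margin |
|---|---|---|---|
| 95% (n = 73) | 92.0% | 83.4% | 113; 213 |
| 90% (n = 35) | 85.9% | 75.5% | 47; 72 |

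**6. Bias**

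If change between tests has a non-zero mean, that mean is added to the estimated bias when the reference came first and subtracted when it came later. A mix of earlier and later references may partly cancel in the bias, but the spread remains.

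**The case against.** Several counter-arguments have force.

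- **Size.** The protocol contains no SD for device error or true change, so every percentage above is conditional. Some pairs will be close in time, because patients can be enrolled as they present for the test and scanned soon after consent. This stands, and step 4 reflects it.
- **Direction.** Random change widens the differences and so works against the device. A reader might infer that the open window produces a falsely favourable result. Random change alone does not, and the protocol gives no direction or size for any systematic change.
- **Stroke volume and cardiac output.** A reader might infer that inflated limits of agreement will be reported for these too. I.2 specifies such limits only for LVEF, so for the other two the claim is confined to the differences.
- **Missing dates.** A reader might infer that test dates are not collected. F.2 refers to an attached data form that is not shown, so this cannot be asserted. The list of variables to be shared with the outside institution (section M) does not include test dates or the interval.
- **Real-world aim and an unseen SAP.** The 30-day limit may be a deliberate pragmatic choice, and covariate detail can sit in an SAP. But eligibility, scan timing and the analysis set are fixed in this protocol. Excluding pairs by interval would contradict I.2 as written. The 30-day rule also shows that an old reference was seen as a problem, and no reason is given for leaving the other cases open.
- **Timing.** The version is dated 29 November 2021, F.1 expects completion in December 2021, and section M speaks of the study in the past tense. Changes to enrollment may come too late; changes to the analysis set need not.

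**Conclusion.** The point holds. As written, the protocol admits pairs that are not contemporaneous into the primary accuracy estimate and reads true change as device error. It applies to LVEF against a past TTE (within 30 days) or a future TTE (no limit), and most clearly to stroke volume and cardiac output against catheterization, where no interval exists in either direction.

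The size is unknown. If change affects every pair, is independent of device error and has an SD of 0.5 to 1 times the device-error SD, the SD of the differences and the LVEF limits widen by 12% to 41%. If half the pairs show negligible change, the range is 6% to 22%. A shift in bias requires change that is mainly in one direction; the protocol makes that possible but gives no evidence that it occurs.

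**What to change.** - State in D.1 and F.2 a maximum scan-to-reference interval, before and after, for each reference test. The investigators should set and justify the lengths, with the shortest for stroke volume and cardiac output against catheterization. Reconcile D.1 and F.2 on whether a past catheterization qualifies.
- Take the date and time of both tests from the records, and add the interval to the variables shared under section M.
- Amend I.2 so that the primary agreement set is the pairs within the stated interval. Fix the interval before the differences are examined.
- Report all other pairs as a secondary analysis, with the interval (signed for order) as a covariate in the regression of the differences that I.2 already plans.
- If enrollment is complete, apply the same rule as a restriction of the analysis set wherever test dates and times can be retrieved.

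The cost is an amendment to the wording, some record retrieval and fewer pairs in the primary set. The number within the interval should be checked against the 73 and 35 evaluable patients that I.2 requires.
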